**4.5. Deep inspiration avoidance before methacholine inhalation enhances the fall of FEV1 in athletes.**

## **5. METHODS**

### **5.1 Study design**

Visits will be done by athletes to the laboratory on 2 occasions each year over a period of at least 3 years and field-tests at 2 times per year according to the annual planning schedule of each team, including 1 testing during competing season and 1 in the resting period. (For example, speed skaters begin their season in September and their resting period is in the month of April.) On the

first visit, consent form will be explained by the investigator or his/her delegate and signed by the subject. At the first visit, physical examination, medical questionnaire regarding their health condition, their family history of disease, their medication and their history in practicing their sport will be performed. Also, respiratory questionnaire, blood sample, eucapnic hyperventilation test, allergy prick skin test, methacholine challenge with Borg score and sputum analysis will be done, as well as the Holter. At the second visit maximal aerobic capacity test and MAPA will be done. At the third visit, spirometric field testing will be performed for each sports. Visit 4, 5 and 6 will be the same as visit 1, 2 and 3, except for allergy test which will be done only on the first visit.

| Visits                                 | 1 | 2 | 3 | 4 | 5 | 6 | 7 | 8 | 9 |
|----------------------------------------|---|---|---|---|---|---|---|---|---|
|                                        |   |   |   |   |   |   | X |   |   |
| Reading and signature of the assent    | X |   |   |   |   |   |   |   |   |
| Physical exam                          | X |   |   | X |   |   |   |   |   |
| Medical questionnaire                  | X |   |   | X |   |   |   |   |   |
| Anthropometric parameters              |   | X |   |   | X |   |   |   |   |
| VO2max test with ECG                   |   | X |   |   | X |   |   |   |   |
| Blood sample                           | X |   |   | X |   |   |   |   |   |
| Respiratory questionnaire              | X |   |   | X |   |   |   |   |   |
| Eucapnic hyperventilation test         | X |   |   | X |   |   |   |   |   |
| Allergy tests                          | X |   |   |   |   |   |   |   |   |
| Methacholine test + Borg score         | X |   |   | X |   |   | X | X | X |
| Induced sputum                         | X |   |   | X |   |   |   |   |   |

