| Spirometric field testing              |   |   | X |   |   | X |   |   |   |
| Holter (heart rate variability)        | X |   |   | X |   |   |   |   |   |
| MAPA (24hre blood pressure monitoring) |   | X |   |   | X |   |   |   |   |

**In an addition, volunteer athletes will have three supplementary visits during the summer season, inside 10 days (visit 7, 8 and 9). These three visits will include different methacholine challenge protocols. The first methacholine challenge (visit 7) will be the same than in the first visit of the excellence protocol (see Table above, standard Juniper protocol), but no**

eucapnic voluntary hyperventilation challenge will be performed before. During the visit 8, a single-dose methacholine will be performed without previous deep inspiration during 20 minutes before the first inhalation. During the visit 9, a single-dose methacholine will be performed without deep inspiration avoidance. These protocols were previously used in asthmatic, control and obese subjects (Simard et al. 2005, Boulet et al. 2005).

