**Methacholine challenge:**

- Methacholine responsiveness will be measured using the “classical” tidal volume method described by Juniper. Briefly, concentrations of methacholine up to 128 mg/ml will be used. Response will be expressed as the PC20 methacholine. Before each FEV1 manoeuvre, the Borg score for perception of breathlessness will be recorded. FVC will also be noted at baseline and after the lowest post-methacholine FEV1.
- During the visit 1, the methacholine challenge is performed after the eucapnic voluntary hyperventilation challenge. During the visit 7, the same methacholine challenge is performed but without previous eucapnic voluntary hyperventilation challenge.
- During the visit 8, a single-dose methacholine test will be performed. Baseline FEV1 will be measured in triplicate and the lowest baseline value will be retained to estimate the percentage fall of FEV1. There will be no saline inhalation. The dose of methacholine chosen for the test will be the final dose that will have induce a 20% fall in FEV1 on methacholine of the visit 7. FEV1 will be measured only at 3 and 4 minutes from the end of the inhalation. At the end of the inhalation, the patient will continue to avoid deep inspiration for three minutes after which the first FEV1 will be obtained.
- During visit 9, the same test as in visit 8 will be performed, except that after baseline measures of FEV1, the inhalation of a single dose of methacholine will be preceded by 20 minutes of deep inspiration avoidance. During that period, the athletes will avoid any deep inspiration including sneezing, coughing, laughing or any abnormal respiratory movement for 20 minutes before the onset of the inhalation of the single dose of methacholine. To ensure that no deep inspiration will be taken, the respiratory volume will be checked with a pneumotachograph.

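### Both descriptions of the deep-inspiration sub-study fix one order of the two single-dose methacholine conditions, and contradict each other on which; either way the avoidance effect is aliased with visit order

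*Protocol*

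**What the plan says.** Hypothesis 4.5 reads "Deep inspiration avoidance before methacholine inhalation enhances the fall of" FEV1, and specific objective 3.2.7 asks the same question. Volunteers attend "three supplementary visits during the summer season, inside 10 days (visit 7, 8 and 9"). Visit 7 is the standard incremental challenge. Visits 8 and 9 are single-dose challenges at the dose taken from visit 7, one with and one without 20 minutes of avoidance beforehand. Their comparison is the test of the hypothesis.

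The protocol describes these two visits twice:

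- **Section 5.1, visit 8:** "a single-dose methacholine will be performed without previous deep inspiration during 20 minutes before the first inhalation". This is the avoidance condition.
- **Section 5.1, visit 9:** "During the visit 9, a single-dose methacholine will be performed without deep inspiration avoidance".
- **Section 4.4.1, visit 8:** "During the visit 8, a single-dose methacholine test will be performed", with no avoidance period before inhalation described. After inhalation, however, "the patient will continue to avoid deep inspiration for three minutes after which the first" FEV1 is taken.
- **Section 4.4.1, visit 9:** "During visit 9, the same test as in visit 8 will be performed, except that after baseline measures" there are 20 minutes of avoidance before the dose.

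Neither section mentions random, alternating or counterbalanced order. Section 4.6 names a Wilcoxon signed rank test for data that cannot be normalised, and no term for visit order. Section 4.5 (Sample size) gives 100 subjects for the whole programme and no number for the sub-study.

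**The concern.** With one sequence for everyone, the avoidance visit is always the second, or always the third, methacholine challenge of the 10-day series. If the response to the same dose moves systematically between those two exposures, the paired difference contains that movement plus any avoidance effect. The movement could look like support for hypothesis 4.5, or it could cancel a real effect, depending on its sign. The order is a design feature, so a statistical analysis plan could not recover the avoidance effect afterwards.

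The contradiction adds to this. It leaves open which way an order shift would act. It also leaves the contrast itself unclear: avoidance before inhalation only, or before and after.

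**Working it through.** There is no figure of the plan's to reproduce: the sub-study has no stated n, effect size, SD or power.

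**1. What the contrast estimates.** Let τ be the effect of avoidance on the percentage fall in FEV1, and π a shift from visit 8 to visit 9 common to all athletes. The mean within-athlete difference, visit 9 minus visit 8, has expectation:

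- section 4.4.1 order (avoidance at visit 9): π + τ
- section 5.1 order (avoidance at visit 8): π − τ

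One equation holds two unknowns in each case. As a matrix check with 20 athletes, the model has 20 athlete columns, one visit-order column and one condition column, so 22 in all. Its rank is 21 under either fixed order, and 22 when half the athletes follow each order.

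**2. What enters π.** Only a shift shared across athletes does. Day-to-day variation that differs at random between athletes has mean zero; it goes into the SD of the paired differences and adds noise, not bias.

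**3. Illustrative size.** Assumed inputs, none of them in the documents: paired SD 6 points of FEV1 fall; n = 12, 20 or 30; common shift 0.5 to 3 points. The true avoidance effect is set to zero, and section 4.6's 95% level is taken as two-sided 5%. The paired t statistic is then non-central t with n − 1 degrees of freedom and non-centrality shift/(6/√n). For a 3-point shift at n = 20 this is 3/(6/√20) = 3/1.342 = 2.236, against a critical value of 2.093, and the rejection probability is 56%.

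| Common shift | n = 12 | n = 20 | n = 30 |
|---|---|---|---|
| 0.5 point | 6% | 6% | 7% |
| 1 point | 8% | 11% | 14% |
| 2 points | 18% | 29% | 42% |
| 3 points | 35% | 56% | 75% |

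The rate rises with n, because more volunteers sharpen the estimate of τ and π combined without separating them.

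**4. Direction.** These rates count rejections on either side, while hypothesis 4.5 is directional. Rejections fall mostly on the side of the shift. If a 3-point shift ran against the avoidance visit, a false result in favour of avoidance would occur less than 0.02% of the time at each n.

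**5. Balanced order.** With n/2 athletes per sequence, the mean differences are π + τ and π − τ. Half their difference is τ. Its standard error is ½√(4 × 6²/n) = 6/√n, the same as in the fixed-order design, with n − 2 degrees of freedom in place of n − 1. In a simulation with n = 20 and a shift of 0.5 SD (3 points at SD 6), the type I error was 4.7%.

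**The case against.** The strongest reply is that the design already limits drift. The three visits fall in one summer season within 10 days. Baseline FEV1 is re-measured in triplicate, and the response is a percentage fall, which removes part of any change in resting calibre. By the section 5.1 schedule athletes have methacholine challenges at visits 1 and 4 as well as visit 7, so a learning effect between visits 8 and 9 is conjecture. Section 5.1 adds that these protocols were used before in asthmatic, control and obese subjects. The sub-study is also a volunteer add-on serving one of seven specific objectives.

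Much of this stands as a limit on the likely size of the shift. It does not break the aliasing. A new baseline does not correct a change in responsiveness to the same dose, and earlier use of the protocols does not show that order effects are absent. Visit 7 cannot serve as a reference point, because it is an incremental test and not a single dose.

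A reader might infer that day-to-day variation as such biases the contrast; only its systematic part does. A reader might also take the 35% to 75% rates as the sub-study's actual error rate. The documents give no shift, SD or n, and at 0.5 point the excess over 5% is about one to two percentage points.

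**Conclusion.** The point holds as a structural defect. Sections 5.1 and 4.4.1 each fix the order for all volunteers, they fix it in opposite ways, and under either one the only contrast that tests objective 3.2.7 and hypothesis 4.5 cannot separate avoidance from visit order and exposure number. That conclusion needs no assumed figure.

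The harm is not known. Under the assumptions shown, false rejection runs from barely above 5% to about 75%, and it supports the hypothesis only if the shift favours the avoidance visit. A shift the other way would work against finding a true effect; the documents give nothing from which to size that loss. It would go too far to say that a positive result is probably an order artefact: the documents support neither the presence nor the sign of a shift, only that the design could not tell. The change is worth making because the aliasing cannot be repaired once the data are collected and its prevention is nearly free.

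**What to change.** 1. Reconcile section 5.1 with the Methacholine challenge text in section 4.4.1, so that the two single-dose conditions are defined once. State for each condition what applies before inhalation and what applies in the minutes after it. Randomisation cannot be set up until this is settled.
2. Keep visit 7 first, because it supplies the dose. Neither single-dose visit uses the other's result, so nothing stated requires a fixed order of the two.
3. Randomise volunteers 1:1 to the order of the two conditions across visits 8 and 9, and record the sequence.
4. Analyse the within-athlete difference with a period term. This removes a shift common to all athletes; it would not remove a carry-over that differs between the conditions.

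The cost is a short randomisation list, one model term and one degree of freedom. No visits, tests or participants are added.

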#### **4.4.2. Cardiac evaluation**

**Blood sample:** A blood sample (46 mL) will be obtained for metabolic parameters described at section 4.3.3.

**Maximal aerobic capacity test:** Maximal oxygen consumption ( $\text{VO}_{2\text{max}}$ ) will be evaluated using a progressive a maximal aerobic capacity test (RAMP). The RAMP protocol consists of an increase in work capacity at each second until the subject cannot continue. This protocol was selected, in order that each subject can reach its  $\text{VO}_{2\text{max}}$  in approximately ten minutes. The  $\text{VO}_{2\text{max}}$  will be considered when a plateau of  $\text{VO}_2$  will be observed in spite of the increase in work capacity (unable to increase  $\text{VO}_2$  by more than 150 ml/min with the increase in the capacity for work), the heart rate will not increase any more in spite of the rise in the intensity of the exercise and/or when  $\text{RER} > 1.15$ . This test will be carried out on a ergocycle or treadmill, depending of which one is closer to the athletes' sports. During this test, each subject will breathe trough a mouthpiece connected to gas analyser and their nose will be occluded by using a nose-clip. The gas exchange will be collected by the gas analyser, making it possible to obtain for each breath, measurements of  $\text{VO}_2$  and  $\text{VCO}_2$ , ventilation ( $\text{V}_\text{E}$ ), ventilatory equivalents in oxygen ( $\text{V}_\text{E}/\text{VO}_2$ ) and in carbon dioxide ( $\text{V}_\text{E}/\text{VCO}_2$ ), respiratory exchange ratio (RER) as well as the ventilatory threshold. A spirometry will also performed before and 1, 5, 10, 15, 20, 25 and 30

minutes after the tests to quantify bronchoconstriction. Heart rate and blood pressure will be continuously monitored.

**Heart rate variability:** The heart rate variability will be obtained from a 24-hours Holter recording for each participants. During this period, the patients will continue their daily activities normally. The parameters of the temporal and the frequency domain will be derived from the 24-hours Holter measures. Some of these parameters (r-MMSD, p-NN50 and high frequency) are indices of the activity of the parasympathetic autonomous nervous system. Other parameters such as the SDNN and the low frequency are indices of the activity sympathetic and parasympathetic nervous system autonomous. The 24-hours Holter recording will make it possible to determine if there is an imbalance between the activity of the autonomous nervous system cardiac sympathetic nerve and parasympathetic among subjects.

**Blood pressure monitoring:** Monitoring of 24-hours blood pressure. This recording will make it possible to assess in a noninvasive way the average blood pressure over 24 hours and the average blood pressure during the day and the night period for the subjects. Blood pressure will be measured every 15 minutes during the day and every 30 minutes during the night.

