#### **3.2 Specific objectives**

- 3.2.1 Determine seasonal and long-term changes in airway caliber, airway responsiveness to methacholine and inflammation in high-level athletes involved in long-term intense training.
- 3.2.2 Evaluate the perception of respiratory symptoms after various airway challenges and evaluate if there is discordance between subjective and objective assessment.
- 3.2.3 Assess the efficacy of asthma medications in asthmatic athletes.

3.2.4 Assess R-R variability in high-level athletes overtime.

3.2.5 Assess cardiac activity in high-level athletes.

3.2.6 Evaluate maximal aerobic capacity in high-level athletes.

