### **5.2.1 Inclusion criteria**

#### All subjects

1. All subjects will provide a written informed consent and the study will be approved by the institutional ethics committee.
2. Subjects will be aged from 18 to 45 years.
3. Athletes will be training for at least 10 hours per week.

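### Whole-day heart rate variability for objective 3.2.4 is confounded with the training done on the recording day, which the protocol neither standardises nor records

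*Protocol*

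**What the plan says.** Objective 3.2.4 in the Protocol is: "Assess R-R variability in high-level athletes overtime". Section 4.4.2 sets out how this is measured:

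- Source: "The heart rate variability will be obtained from a 24-hours Holter recording for each participants".
- Conditions: "During this period, the patients will continue their daily activities normally".
- Derivation: "The parameters of the temporal and the frequency domain will be derived from the 24-hours Holter measures".
- Interpretation: RMSSD (written r-MMSD there), pNN50 and high frequency are read as parasympathetic indices, and SDNN and low frequency as mixed ones. The stated purpose is: "The 24-hours Holter recording will make it possible to determine if there is an imbalance between the activity of the autonomous nervous system", followed by a reference to comparison among subjects.

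Section 5.1 gives the timing. The yearly plan follows each team's calendar, "including 1 testing during competing season and 1 in the resting period". At visit 1, "methacholine challenge with Borg score and sputum analysis will be done, as well as the Holter". Visit 4 repeats visit 1 apart from the allergy test, and the schedule table marks the Holter at visits 1 and 4.

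Two other places bear on training. An entry condition in section 5.2.1 reads: "Athletes will be training for at least 10 hours per week". Section 4.4.1 has a questionnaire item on how long athletes train outdoors and indoors, but it is not tied to the day of the Holter.

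**The concern.** A normal day for these athletes can include hours at a high heart rate. SDNN over a whole day contains the spread between exercise and non-exercise heart rates, so it depends on how much of the day was spent training even when autonomic control is unchanged. Whole-day RMSSD and high-frequency power are diluted by exercise beats, which carry little vagal modulation.

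The two testing periods are chosen because sporting load differs between them. Training on the recording day can therefore be expected to differ systematically by period, and a bias of that kind does not shrink with the 100 athletes planned. The comparison among subjects is affected as well, because an athlete recorded on a training day is not comparable with one recorded on a day off.

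The danger is one of interpretation. SDNN and RMSSD move in opposite directions when training is added to the day. A reader following section 4.4.2 could take that pattern for a shift in autonomic balance. If the day's training is not noted at the time, it may not be recoverable later.

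**Working it through.** The Protocol states no HRV effect size, standard deviation or power, so there is no figure to reproduce. The calculations below are illustrations. They hold autonomic state fixed and change only the training content of the day.

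**Input from the documents.** The entry minimum is 10 h per week, so 10/7 = 1.43 h per day on average, or 1.43/24 = 6.0% of the recording.

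**Assumed inputs, first model.** Mean R-R is 1000 ms outside training and 60,000/140 = 429 ms in training (140 bpm). SDNN within each state is 120 or 180 ms.

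**Formulas.**
- p = training beats / all beats
- between-state SD = √(p(1−p)) × (1000 − 429)
- 24-hour SDNN = √(within² + between²)

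**Worked case, 1.43 h.** Training beats are (10/7) × 60 × 140 = 12,000. Other beats are 22.57 h × 3,600 = 81,257. So p = 12,000/93,257 = 0.129, the between-state SD is 191 ms, and SDNN is √(120² + 191²) = 226 ms or √(180² + 191²) = 263 ms.

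| Training that day | p | Between-state SD (ms) | SDNN, within 120 (ms) | SDNN, within 180 (ms) |
|---|---|---|---|---|
| none | 0 | 0 | 120 | 180 |
| 0.71 h | 0.067 | 143 | 186 | 230 |
| 1 h | 0.092 | 165 | 204 | 244 |
| 1.43 h | 0.129 | 191 | 226 | 263 |
| 2 h | 0.175 | 217 | 248 | 282 |

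**Spurious change in SDNN.**
- 2 h against 1 h: 248/204 = +21%; 282/244 = +15%.
- 1.43 h against half that (0.71 h): 226/186 = +21%; 263/230 = +14%.
- 1.43 h against none: 226/120 = +88%; 263/180 = +46%.
- 1.43 h against none, with training at only 120 bpm (R-R 500 ms): SDNN 198 and 239 ms, or +65% and +33%.

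**Second model, with sleep separated (all segment values assumed).**
- Day without training: 16 h awake (mean R-R 950 ms, SD 110, RMSSD 50) and 8 h asleep (1250 ms, SD 100, RMSSD 80). This gives 24-hour SDNN of 172 ms and RMSSD of 60 ms.
- Day with training: 1.43 to 4 h of waking time becomes training (450 ms, SD 50, RMSSD 6), with or without 2 h of recovery (750 ms, SD 80, RMSSD 25). SDNN becomes about 255 to 317 ms (+49% to +85%). RMSSD becomes about 49 to 57 ms (−6% to −18%).
- The sleep values are the same throughout, by construction.

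No figures were computed for pNN50, low frequency or high frequency.

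**The case against.** Several points on the other side have force.

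- **The season contrast is not written out for HRV.** Objective 3.2.1 speaks of seasonal change, but for the airways. Objective 3.2.4 asks only about change over time, and section 4.4.2 speaks of differences among subjects. A year-to-year comparison within the same season would remove much of the systematic part. This stands: the contrast is inferred from objective 3.2.4 and section 5.1. Even so, training on the day remains uncontrolled in every comparison the Protocol names.
- **The recording is not only training.** A reader might infer that the seasonal change would measure the day's training rather than autonomic adaptation. The documents do not support that. The 24 hours also cover sleep and non-training time, so the change is a mixture, and the indices that section 4.4.2 calls parasympathetic are likely to be less affected than SDNN.
- **The bronchial challenges.** A reader might infer that hyperventilation and methacholine on the Holter day create a difference between periods. They are scheduled at both visits 1 and 4, so they are a common disturbance and do not by themselves create a period effect. The Protocol also does not say whether the recorder is fitted before or after them.
- **The large SDNN figures use a zero-training comparator.** The Protocol does not say that athletes stop training in the resting period. This stands, and it is why the 1 h against 2 h contrast is shown.
- **The analysis window could be set in an analysis plan that is not shown.** This is true of the window. The recording conditions, however, are fixed in this Protocol, and no analysis plan can recover training that was never noted. The general questionnaire item in section 4.4.1 does not supply it.

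**Conclusion.** The point holds as a matter of confounding. Whole-day HRV, SDNN above all, depends on training during the recording, and the Protocol neither standardises nor records that training. A change over time or a difference among athletes cannot then be attributed to autonomic state.

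Under the assumed R-R values, the spurious SDNN change is about +15% to +21% for a difference of one hour in training (1 h against 2 h). It reaches about +46% to +88% for none against 1.43 h. The RMSSD shift is about −6% to −18% for 1.43 to 4 h against none. These sizes rest entirely on assumed inputs. They show that same-day training alone can produce an apparent effect, and they do not show that it would explain all of one.

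HRV is one of several objectives in a largely descriptive cohort, so this does not threaten the study as a whole. It is worth correcting because section 4.4.2 gives the indices an autonomic meaning and the correction is cheap.

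**What to change.** In section 4.4.2 of the Protocol, under heart rate variability:

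1. Name the night (sleep) segment of the same Holter as the main source of SDNN, RMSSD, pNN50, low frequency and high frequency for objective 3.2.4. This also reduces the influence of the challenges done on the visit day. Section 4.4.2 already summarises blood pressure separately for day and night, so the split fits the Protocol's own practice.
2. Keep the whole-24-hour values as descriptive results.
3. Record the training done on the Holter day, in hours and clock time, at every recording. Use it as a covariate or to describe results by training content.

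No extra attendance is needed. The cost is a few lines of text, one log entry per recording and a different analysis window on data already collected. The downsides are fewer beats per recording and the move of whole-day SDNN to a secondary place. Some carry-over of the day's training into sleep may remain, so the log is needed as well as the night window.
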